Given this background, the main aims of this study are firstly, to investigate the changes in physical performance and glycemic control 4 weeks after initiation of guideline-directed medical therapy of an SGLT2i and exercise therapy in patients with established ASCVD or high cardiovascular risk and T2D with initial inadequate glycemic control; secondly, to investigate the changes in physical performance and glycemic control 4 weeks after exercise therapy only in patients with established ASCVD or high cardiovascular risk and T2D with adequate glycemic control; thirdly, to investigate the changes in physical performance 4 weeks after exercise therapy only in non-diabetic patients with established ASCVD or high cardiovascular risk; and fourthly to investigate the cross-sectional and longitudinal association of glycemic control at baseline and new guideline directed antidiabetic treatment (inadequate glycemic control and diabetes + new SGLT2i vs adequate glycemic control and diabetes vs. no diabetes) with physical performance and other outcomes influencing physical performance (secondary outcomes), in patients with established ASCVD or high cardiovascular risk after adjusting for baseline covariates.

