##### Body-mass-index

Body mass index (BMI) in kg/m^2^ measured as weight (kg) divided by measured height (m) squared. Weight and height were measured upon admission by blinded certified nurses and physiotherapists, respectively, and entered into patient records. During stay, weight was controlled at regular intervals in the morning before breakfast during the clinical visits by blinded nurses.

BMI is a crude adiposity indicator with higher BMI being an independent predictor of higher mortality risk in the general population (76, 77). On the other hand, many large cohort studies of individuals with T2D and high BMI suggest higher BMI to be a protective factor for all-cause mortality, a phenomenon described as the “obesity paradox” (81–83). Consequently, in interventions inducing weight reduction in individuals with T2D, such as regular exercise training in rehabilitation in combination with diet and SGLT2 is, lifestyle changes focussed around improving physical performance are recommended to alleviate the potential risk of BMI reduction and cardiovascular mortality (84, 85).

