##### Anthropometric-indices

Anthropometry comprising of mean waist and hip circumferences in cm, waist-to-height, and waist-to-hip ratios. Waist circumference was measured during the clinical examination by treating rehabilitation physicians at the level of the umbilicus with the patient standing erect and feet together.Waist circumference has been demonstrated to be a modifiable factor associated with post-rehabilitation physical performance and function (110). Additionally, both waist-to-height and waist-to-hip ratios have been associated with cardiovascular events (111–113).

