#### Data analyses

Demographic data will be examined using independent-samples *t*-tests and Fisher's exact tests for dichotomous variables. Independent-samples *t*-tests and repeated-measures ANOVAs will be employed to compare changes in physical performance after 4 weeks. Differences between primary and secondary outcome variables after 4 weeks will also analyzed by linear mixed-effects models (LMMs). The time factor for the model will be set at baseline and week 4. The models will include model-based adjustments for baseline characteristics influencing physical performance in such cohorts: (1) age, sex, BMI, waist circumference, diabetes duration and history of cardiovascular disease.

To minimize the bias that could result from participants in the 3 groups having highly variable duration of stay, the prospective analyses will be performed on a modified intention-to-treat and per protocol basis. The modified intention-to-treat population will be defined as participants who have been categorized to a study group and have at least one follow-up measurement of the primary outcomes, regardless of treatment adherence or duration of stay. The “last observation carry-forward method” will be used in the absence of complete follow-up data. For “per protocol” analysis, only those participants who have follow-up measurements after a minimum treatment duration or length of stay of ≥20 days will be included.

Sensitivity analyses will be performed to account for potentially non-ignorable missing data due to dropout as well as the possible impact of other potentially influential variables. A Bonferroni correction will be applied to the LMM analyses of the primary and secondary outcomes.

Pre-specified subgroup analyses will be conducted; these will include subgroups defined according to the various entities of ASCVD, gender, age groups, and other factors.

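### BMI and waist circumference are on the covariate list for models in which they are also the outcome, so their adjusted baseline group difference is zero or nearly zero whatever the data show

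*Protocol article*

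**What the plan says.** Four statements in the protocol article bear on this.

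- Data analyses sets the scope of the models: "Differences between primary and secondary outcome variables after 4 weeks will also analyzed by linear mixed-effects models (LMMs"). It fixes their time points: "The time factor for the model will be set at baseline and week 4". The baseline value is therefore one of the two responses.
- The same paragraph gives the adjustment: "The models will include model-based adjustments for baseline characteristics influencing physical performance in such cohorts", followed by the list "age, sex, BMI, waist circumference, diabetes duration and history of cardiovascular disease". The list is given once, for the models in general.
- Under Secondary outcomes, the Body-mass-index entry reads "Body mass index (BMI) in kg/m^2^ measured as weight (kg) divided by measured height (m) squared" and the Anthropometric-indices entry reads "Anthropometry comprising of mean waist and hip circumferences in cm, waist-to-height, and waist-to-hip ratios". BMI, waist circumference and two ratios built from waist are thus outcomes.
- The fourth aim in the Introduction is "to investigate the cross-sectional and longitudinal association of glycemic control at baseline" and new treatment with physical performance and with "other outcomes influencing physical performance (secondary outcomes), in patients with established ASCVD or high cardiovascular risk after adjusting for baseline covariates". An adjusted baseline comparison of the secondary outcomes is therefore a stated aim.

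No other covariate list appears in the article, and no outcome is exempted from this one.

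**The concern.** Two variables have both roles at the same time point. When baseline BMI is the response and baseline BMI is also a regressor, the regressor explains the response completely and nothing is left for group. The same holds for waist. The resulting estimate carries no information about whether the groups differ at baseline, although that comparison is part of the fourth aim and body size may well differ between participants with and without diabetes. What is at stake is the adjusted baseline contrast for a few body-size secondary outcomes.

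**Working it through.** The plan states no figure to reproduce here. The question is one of model structure. Let B be baseline BMI, D the change to week 4, ΔB and ΔD the group differences in B and D, and s the within-group slope of D on B.

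**1. Cross-sectional model.** Regress B on group, B and the remaining covariates. Least squares fits perfectly with a coefficient of 1 on B and 0 on everything else. The group coefficients are exactly 0 for any data. The same algebra applies to waist.

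**2. Mixed model, one common slope for B.** The responses are B and B + D, with group, time and group-by-time terms. In complete pairs the covariate slope is the within-group slope of the average response, B + D/2, on B, which is 1 + s/2. The adjusted baseline contrast is then

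ΔB - (1 + s/2)ΔB = -(s/2)ΔB.

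This is close to zero but equals zero only if s = 0.

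**3. Mixed model with covariate-by-time terms.** The baseline rows have their own slope, which is 1, so the baseline contrast is exactly 0 again.

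**4. Numerical check.** The documents give no BMI values, so these are assumptions: baseline means 31, 29 and 27 kg/m² in Groups I, II and III; SD 5; waist correlated with BMI; mean change -1.0, -0.5 and -0.4 plus s times (B - 29), SD 0.8; age and sex as further covariates. There are 150 per group, as in the Sample size section, in one simulated data set. The raw baseline differences in the sample were -1.746 (II minus I) and -3.459 (III minus I).

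- Cross-sectional model with the list as written: 0.000 and 0.000, coefficient of BMI 1.000.
- Mixed model without BMI and waist: about -1.72 and -3.46, so the raw differences are recovered.
- Mixed model with BMI and waist, common slope:

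| s | slope 1 + s/2 | fitted slope | II-I: formula | II-I: fitted | III-I: formula | III-I: fitted |
|---|---|---|---|---|---|---|
| 0 | 1.000 | 0.9995 | 0 | 0.008 | 0 | 0.023 |
| -0.03 | 0.985 | 0.9845 | -0.026 | -0.019 | -0.052 | -0.029 |
| -0.1 | 0.950 | 0.9495 | -0.087 | -0.080 | -0.173 | -0.150 |
| -0.3 | 0.850 | 0.8495 | -0.262 | -0.254 | -0.519 | -0.496 |

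The constant gap between formula and fit (about 0.008 and 0.023) is sampling noise, since the same random draws were used in each row. At s = -0.3 the surviving share is 0.496/3.459 = 14%.

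**5. Four-week change.** In the common-slope model the group-by-time estimates are the same with and without BMI and waist: 0.617 and 0.724 at s = 0, and 1.141 and 1.762 at s = -0.3. With covariate-by-time terms they become the baseline-adjusted change (0.633 and 0.770 at every s), a different but proper quantity.

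**6. Waist ratios.** Height and hip circumference are not on the list, so no algebraic zero applies. In separate simulations of the Group I versus III contrast, also on assumed values, a waist-to-height difference of 0.055 fell to 0.000 when height was balanced between groups. When Group I was assumed 3 cm shorter, 0.010 of 0.061 remained. Waist-to-hip was not computed.

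**The case against.** The strongest reply is that the exact zero comes from joining two places. Data analyses attaches its list to mixed models of differences after 4 weeks and does not write out a cross-sectional model. The fourth aim does not name its covariates. The Study design section describes the cross-sectional and prospective analyses for physical performance, and the covariates are justified by their influence on physical performance. A condensed article may leave the rest to a fuller document. An analyst would also notice a model with zero residual.

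Part of this stands. The article does not write down the cross-sectional model for BMI or waist, and nothing suggests that a degenerate fit would be published as evidence of no association. Two things remain. The covariate sentence follows directly on sentences that cover primary and secondary outcomes together, and it is the only list in the article for an aim that explicitly includes the secondary outcomes. And the mixed model that Data analyses does specify already collapses the baseline contrast, without help from the aims.

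A reader might also infer that the adjusted week-4 difference is wrong because it can change sign. At s = 0 in the simulation, the III minus I contrast at week 4 goes from -3.455 + 0.724 = -2.731 without BMI and waist to 0.023 + 0.724 = 0.747 with them. That is not an error. It answers another question: how the groups differ at week 4 for the same starting BMI. This is a legitimate estimand.

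**Conclusion.** The point holds and is minor. If the list is applied as written, the adjusted baseline group difference in BMI and in waist is exactly zero in the cross-sectional model, with no assumption about the data. In a common-slope mixed model it is about -(s/2) times the raw difference, so at most about 15% of it survives for s between 0 and -0.3; that range of s is assumed. Waist-to-height and waist-to-hip contrasts are attenuated by an amount that cannot be fixed in advance.

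Three stronger readings are not supported. The mixed-model contrast is not zero by construction under a common slope. The waist ratios are not forced to zero. And neither the primary outcomes nor the 4-week change estimates are undermined: no primary outcome is on the covariate list, and the group-by-time estimates in the common-slope model are unchanged in complete pairs.

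**What to change.** Add one sentence to Data analyses: a covariate is omitted from any cross-sectional or repeated-measures model in which it is the outcome or a direct component of the outcome. This means BMI is dropped when BMI is the outcome, and waist circumference is dropped for waist, waist-to-height and waist-to-hip. Where adjustment for the starting value is wanted, use the week-4 value alone as the response with the baseline value as covariate, so that baseline is not also a response row.

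There is no need to drop both BMI and waist from every body-size model. Baseline BMI adjusted for waist is not degenerate: in a simulation on assumed values, 0.94 of a 3.92 kg/m² difference remained.

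The change needs no new data or participants. Its only cost is a slightly different covariate list for these few outcomes.

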#### Inclusion criteria

Ambulatory patients, defined as able to walk about and not bedridden, with or without walking aids admitted following a medical or surgical condition warranting inpatient rehabilitation,willing to give informed written consent,with established ASCVD or high cardiovascular risk with and without T2D were included. ASCVD and high cardiovascular risk were defined as follows:

a. established ASCVD: coronary artery disease (CAD), cerebrovascular disease (CeVD), peripheral artery disease (PAD) and ischemic congestive heart failure (CHF),b. high cardiovascular risk: as defined in the 2016 European Guidelines on cardiovascular disease prevention in clinical practice (13). consisting of patients without clinically manifest ASCVD with markedly elevated single cardiovascular risk factors (hypertension with blood pressure ≥180/110 mmHG, blood lipid profile with cholesterol > 8 mmol/L, metabolic syndrome and central obesity with body mass index ≥40 kg/m^2^ in patients below 60 years of age), or with T2D plus any additional risk factor, or with moderate chronic kidney disease defined as glomerular filtration rate between 30 and 59 mL/min/1.73 m^2^, or with a calculated systematic coronary risk estimation (SCORE) ≥5 and <10 % (13), or with scores above the high risk cut-off using the American College of Cardiology (ACC)/American Heart Association (AHA) score of ≥20% (34, 35).

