### Study group categories

Glycemic control was assessed within the first 3 days upon admission by measurement of fasting plasma glucose (FPG) with the widely used diagnostic cut-off of ≥7 mmol/L employed to define inadequate glycemic control (33, 36). Hemoglobin A_1c_ (HBA_1c_) testing was equally done in all participants upon admission but was not used to define inadequate glycemic control in this cohort to circumvent the bias linked to participants with conditions that affect erythrocyte turnover such as acute bleeding and/or erythrocyte transfusion during the acute hospitalization prior to rehabilitation (33). HbA_1c_ was however used as one of the parameters to distinguish participants with diabetes or impaired glucose metabolism from those with normal glucose metabolism as described below.

Depending on their glycemic control upon admission and following guideline recommendations, participants were categorized to one of three groups using clinically defined cut-off categories of FPG levels as follows (11):

Group I: Participants with inadequately controlled T2D defined as mean FPG of ≥7 mmol/l within the first 3 days upon admission under other standard of care medication, who were afterwards administered *de novo* SGLT2i treatment; namely either canagliflozin 100 mg, or dapagliflozin 10 mg, or empagliflozin 10 mg once daily, with the choice of which of the SGLT2is being at the discretion of the individual treating physician,

Group II: Participants with adequately controlled T2D, previous diagnosis of T2D or use of antidiabetic medication, with mean FPG <7 mmol/L; and participants with impaired fasting glycemia (IFG) or pre-diabetes, defined as mean FPG of 5.6–6.9 mmol/L and HbA_1c_ levels of 5.7–6.4 % (15, 33), under other standard of care treatment and no SGLT2i,

Group III: Participants with no previous diagnosis of T2D or use of antidiabetic medication and normal glucose metabolism defined as FPG of ≤ 5.5 mmol/L under other standard of care treatment and no SGLT2i were included as a reference group as previously described in the meta-analysis of prospective studies on diabetes mellitus, FPG, and risk of vascular disease (11).

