### Outcome measures: Assessment, blinding, and rationale

The PUSH assessed objective and subjective outcomes of physical performance in addition to hemodynamic, cardiorespiratory, and cardiometabolic risk variables. Outcome assessments were done upon admission (baseline), facultatively at week 2 and at week 4 (Table 1). All participants, direct care providers and assessors were masked to the outcomes under investigation throughout the study. Whereas, participant and care providers were blinded by categorically withholding supplementary information on the glycemic control categories described above and exposures under investigation, main outcome assessors (therapists and laboratory technicians) were masked by complete prohibition of access to patient medication data as per previously established institutional policy.

**Table 1 T1:** Assessment time plan.

**Assessment**	**Time points during study**		
	**Baseline** ^a^	**Week 2**	**Week 4**
Screening for inclusion and exclusion criteria	°		
Participant characteristics^b^	°		
Status of medications^c^	°	°	°
Anthropometric and clinical parameters^d^	°	°	°
Laboratory tests^e^	°	°	°
Rehabilitation outcomes^f^	°	°	°
Transthoracic echocardiography^g^	°		°
Sonographic assessment of liver parenchyma (NAFLD)^h^	°		°
Muscle sonography^i^	°	°	°
Monitoring for adverse events^j^	Throughout stay		

a *Baseline was defined as the date of eligibility confirmation and inclusion in the study. If no data were available at baseline, the most recent data from the hospitalization prior to admission were used*.

b
*Included information on age, sex, medical history, complications and comorbidities, smoker status, coffee consumption.*

c
*Included antidiabetic agents, antihypertensives, lipid-lowering drugs, thrombocyte aggregation inhibitors, therapeutic anticoagulation, use of proton pump inhibitors, uric acid lowering drugs, antidepressants, opiates, NSAIDs, neuropathic pain treatment, vitamin D, iron, calcium, and magnesium substitution.*

d
*Included body weight, BMI, waist and hip circumferences, estimation of skeletal muscle mass in kg using the Baumgartner equation, mean systolic and diastolic blood pressures, mean fasting plasma glucose (for all groups at baseline, for group I and II at week 2 and 4), peak expiratory flow rate, state of nocturia, pain numeric rating scale [NRS] (range 1–10).*

e

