The PUSH design however has some limitations. First, the non-randomized design precludes analyses and conclusions of the causal relationships among variables. Second, despite efforts to address the internal validity threats, the selection bias of using glycemic control to determine participants for the guideline-directed medical therapy with an SGLT2i remains an important threat in the interpretation of the results even though a previous study in this field did not show any negative impact of suboptimal glycemic control under treatment with an SGLT2i (dapagliflozin 10 mg) on the physiological adaptation to endurance exercise training (31). Accordingly, studies on changes in physical performance under SGLT2is in patients with both inadequately and adequately controlled T2D are still warranted. Third, the prospective design of this study with a follow-up of just 4 weeks addresses solely the hypothesis of early changes in physical performance under guideline-directed medical therapy with an SGLT2i. Further studies will be necessary to investigate, if present, the extent and sustainability of these early changes over a longer period of observation with or without endurance exercise therapy. Finally, we will not compare participants to those who did not receive inpatient rehabilitation after a medical or surgical condition warranting inpatient rehabilitation, as such, the potentiating effect of exercise therapy during rehabilitation on the results shall not be easily quantified.

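### The named adjustment set omits the condition that led to rehabilitation, so an uneven mix of admission conditions across the non-randomised groups could confound the adjusted difference in 6-MWD gain

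*Protocol article*

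**What the plan says.** The Data analyses section states that "The models will include model-based adjustments for baseline characteristics influencing physical performance in such cohorts" and then lists them: "age, sex, BMI, waist circumference, diabetes duration and history of cardiovascular disease". The time factor has two levels, baseline and week 4, and a Bonferroni correction applies to these models.

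Under Inclusion criteria, ambulatory patients qualify if they have established ASCVD or high cardiovascular risk and were "admitted following a medical or surgical condition warranting inpatient rehabilitation". The exclusion criteria narrow this. They remove, among others, infarction or unstable angina in the previous 4 weeks, active malignancy, marked pain at rest, and terminal conditions that severely limit walking.

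Under Study group categories, membership follows mean fasting plasma glucose in the first 3 days, together with diabetes history and medication. The same section explains that HbA1c was not used to define inadequate control because of conditions such as "acute bleeding and/or erythrocyte transfusion during the acute hospitalization prior to rehabilitation".

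Three other statements bear on the point:
- Data analyses plans sensitivity analyses for dropout "as well as the possible impact of other potentially influential variables", without naming any.
- It plans "subgroups defined according to the various entities of ASCVD, gender, age groups, and other factors".
- The Discussion concedes that "the selection bias of using glycemic control to determine participants for the guideline-directed medical therapy with an SGLT2i remains an important threat".

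Footnote b of Table 1 lists baseline information including "medical history, complications and comorbidities". Neither the admission condition nor the date of the preceding event is listed by name.

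**The concern.** The 4-week gain in a rehabilitation inpatient plausibly has at least two parts: recovery from whatever led to admission, and response to exercise (plus any drug effect in Group I). A cardiac operation, a stroke, an orthopaedic procedure and a medical illness need not share a recovery slope. In a randomised trial that variation would be noise. Here nothing balances it across groups.

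The nearest listed covariate is history of cardiovascular disease. It does vary in this cohort, since patients at high risk without manifest ASCVD are also enrolled. But it describes comorbidity, not the reason for admission. A patient with coronary disease admitted after hip surgery and one admitted after bypass surgery both have that history.

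The inclusion criteria also offer a route by which admission mix could differ. Patients with diabetes can enter without ASCVD through diabetes plus one further risk factor, and Group III cannot use that route. This shows that imbalance is possible. It does not show that it occurred, or in which direction.

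At stake is the study's fourth aim, the association of glycemic category and new SGLT2i treatment with physical performance after adjustment for baseline covariates. A case-mix difference could be read as a group effect.

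**Working it through.** **1. What the text fixes.** The named covariates are age, sex, BMI, waist circumference, diabetes duration and cardiovascular history. Admission condition and time since the event are absent. This is settled by reading.

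**2. Do the other planned analyses cover it?** The sensitivity variables are unnamed. Subgroups by ASCVD entity classify the vascular disease, not the reason for admission. Neither changes the main adjusted estimate.

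**3. Inputs from the Sample size section.** Baseline 250 m; anticipated gain 80 m with SD 40 m; difference to detect 15%; two-sided 5%; 80% power; 130 per group. The base of the 15% is not stated, so two readings are carried:
- 15% of the gain: 0.15 × 80 = 12 m.
- 15% of the baseline: 0.15 × 250 = 37.5 m.

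Neither reproduces 130 per group. With n = 2 × [SD × (1.960 + 0.842) / difference]² and SD 40 m, 12 m needs 175 and 37.5 m needs 18. That mismatch is a separate matter. It matters here only because it leaves the yardstick uncertain.

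**4. Inputs assumed.** The article gives neither gain by admission condition nor case mix by group. Assumed: one category gains 20-40 m more than another (40 m is one stated SD of the gain), and its share differs by 10-20 percentage points between two groups. The listed covariates are assumed to absorb none of this.

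**5. Bias.** Bias = difference in gain × difference in share.
- Low: 20 × 0.10 = 2 m.
- Middle: 20 × 0.20 or 40 × 0.10 = 4 m.
- High: 40 × 0.20 = 8 m.

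Against 12 m: 2/12 = 17% to 8/12 = 67%. Against 37.5 m: 2/37.5 = 5% to 8/37.5 = 21%.

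**6. False-positive risk with no true group effect.** SE = 40 × √(2/130) = 4.96 m, the unadjusted two-group value. Rejection probability = Φ(bias/SE − z) + Φ(−bias/SE − z).

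| Bias | bias/SE | Uncorrected 5% (z = 1.960) | Bonferroni over 3: 1.7% (z = 2.394) |
|---|---|---|---|
| 2 m | 0.40 | 6.9% | 2.6% |
| 4 m | 0.81 | 12.7% | 5.7% |
| 8 m | 1.61 | 36.4% | 21.7% |

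The right-hand column counts only the three primary outcomes. The article applies the correction to secondary outcomes as well. If they share one family, the nominal level and these probabilities fall further. The bias in metres does not change.

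**7. Form of the covariate.** With two time points, a main effect of a covariate shifts baseline and week 4 equally and cancels out of the change. Only an interaction with time adjusts the gain.

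**The case against.** The strongest reply is that any observational covariate list can be lengthened, and that the article shows no contradiction here. That recovery depends on admission condition is plausible, but the article neither says nor quantifies it. The article is also condensed: the covariate list opens with a (1) that has no (2), so a fuller list may exist elsewhere, and how cardiovascular history is coded is a detail often left to an analysis plan. The Discussion says the non-randomised design rules out causal conclusions. The ASCVD-entity subgroups touch the stroke and cardiac cases.

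Much of this stands as a limit on size. It does not remove the point. The article chose to name its adjustment set, and the set as named omits an obvious candidate. The caveat in the Discussion concerns selection by glycemic control, not case mix by admission condition. Subgroup results do not adjust the main comparison.

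Three stronger readings are tempting and not supported:
- A reader might infer that every participant enters fresh from an acute illness of any kind. The inclusion criteria do not say so, and the exclusion criteria narrow the mix.
- A reader might infer that the planned models' error rate rises from 5% to as much as 36%. That ignores the stated Bonferroni correction.
- A reader might infer that admission condition is already a recorded study field. Table 1 does not name it.

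**Conclusion.** The omission is a fact of the text. Its consequence is conditional: it needs recovery rates that differ by admission condition and a case mix that differs by group, and the article documents neither. No direction can be given. The bias and error-rate ranges above illustrate what moderate imbalance would do. They are not estimates for this study, and they would be smaller if the listed covariates pick up part of the case mix. How large the bias looks against the target effect also depends on which base the 15% has.

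A reader should therefore not conclude that the group comparison is confounded, only that the planned main model cannot rule this out. It is a worthwhile, inexpensive improvement to a stated adjustment set, not a demonstrated error in the results.

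**What to change.** Add to the main mixed model:
- admission condition in a few categories (for example cardiac surgery, other surgery, stroke, medical illness);
- where the date can be recovered from the records, days from the event or hospital admission to rehabilitation admission.

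Enter each with a time interaction so that it acts on the gain. Tabulate both by glycemic group, so that readers can see whether any imbalance exists. The categories should be fixed before the group comparison is examined.

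The change concerns analysis only, so the end of data collection in September 2020 does not prevent it. The cost is coding from admission records, since Table 1 does not name these fields and some event dates may be missing, plus a few degrees of freedom in a study of 450 participants.

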### Sample size and data analysis

#### Sample size

Based on the results of the cardiovascular heart study of Enright et al., among 2,281 community dwelling adults ≥68 years old, the expected mean 6-min walk distance (6MWD) was 344 ± 88 m which is the set target of exercise therapy in rehabilitation (45). Centered on our clinical observations and on the results of a small pilot study in the clinical rehabilitation of patients with cerebrovascular disease (121), we assumed a mean 6-MWD at baseline of 250 m with an anticipated improvement of 80 ± 40 m after 4 weeks of exercise therapy. To detect an additional difference of ±15%, as reported in previous studies on this subject (28), within the group as well as between any 2 groups with power of 80 % and an alpha error of 5% using a 2-sided test after 4 weeks, the sample size required was 130 participants per group. Based on our admission statistics, the attrition rate for administrative reasons, mainly being lack of insurance coverage for a treatment duration of at least 20 days, was estimated at 15 %, while 85 % of participants were expected to complete the week 4 follow-up. To this end, 150 participants per group needed to be enrolled (450 participants in total).

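### Both prospective analysis sets are defined by post-baseline events, so participants with no repeat walk test are in neither, although the planned mixed model could keep them

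*Protocol article*

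**What the plan says.** Data analyses gives the purpose of the two sets: "To minimize the bias that could result from participants in the 3 groups having highly variable duration of stay". The modified intention-to-treat (mITT) set consists of "participants who have been categorized to a study group and have at least one follow-up measurement of the primary outcomes, regardless of treatment adherence or" length of stay. For the per-protocol set, "only those participants who have follow-up measurements after a minimum treatment duration or length of stay of ≥20 days will be included". Neither set is named as primary.

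The assessment schedule (Outcome measures: Assessment, blinding, and rationale) reads: "Outcome assessments were done upon admission (baseline), facultatively at week 2 and at week 4".

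On missing data, Data analyses says that last observation carried forward (LOCF) "will be used in the absence of complete follow-up data", and adds: "Sensitivity analyses will be performed to account for potentially non-ignorable missing data due to dropout". For the linear mixed-effects model (LMM): "The time factor for the model will be set at baseline and week 4". Independent-samples t-tests and repeated-measures ANOVAs of change are planned alongside it.

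On expected loss, Sample size says that attrition for administrative reasons, mainly insurance cover for a stay of at least 20 days, "was estimated at 15 %, while 85 % of participants were expected to complete the week 4 follow-up".

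**The concern.** The objectives concern change over 4 weeks in patients categorized at admission. Both sets instead condition on something that happens later: having been retested, or having follow-up measurements after at least 20 days. The mITT set is presented as indifferent to length of stay, yet a participant must stay long enough, and be able, to repeat the walk test. The only scheduled test before week 4 is optional, so a short stay without it leaves no follow-up value. LOCF cannot restore these participants, because it acts only within a set they have not entered.

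If leaving without a retest is related to walking ability or progress, the within-group change (a main objective) describes only those who could be retested. If that relation differs between groups, the between-group difference in change is also affected. The groups are not randomized, and only Group I starts a new SGLT2 inhibitor, so the design does not guarantee equal loss.

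**Working it through.** **1. How many participants are at issue.** Inputs from Sample size: 130 evaluable per group, 15% attrition, 150 enrolled per group.
- The stated enrolment: 130 × 1.15 = 149.5, rounded to 150, reproduces the plan. (Dividing, 130 / 0.85 = 152.9, would give 153; the difference does not matter here.)
- Expected with a week-4 value: 150 × 0.85 = 127.5 per group.
- At risk of exclusion: 150 − 127.5 = 22.5 per group, or 67.5 of 450.

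This is roughly a ceiling for mITT, since leavers with a week-2 or other follow-up test are retained. The article does not give the uptake of the optional test.

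**2. General formula.** Overstatement of a group's mean change = p × D, where p is the excluded share and D is the mean gain in retained participants minus that in excluded participants. If D = 0, the bias is 0 for any p. Between groups with the same D, the bias is the difference in p times D, so equal loss gives 0.

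**3. Loss that depends on baseline walk distance.** Assumptions, not in the article: the probability of no retest follows a logistic model in standardized baseline distance z, with odds ratio 2 to 3 per SD lower and 15% loss overall; z correlates ρ = 0.3 to 0.4 with gain. The SD of gain, 40 m, is from Sample size.
- Overstatement = ρ × 40 × E(z | retained).
- Integrating the logistic model over a standard normal z, E(z | retained) = 0.098 at odds ratio 2 and 0.142 at odds ratio 3.
- Smallest: 0.3 × 40 × 0.098 = 1.2 m. Largest: 0.4 × 40 × 0.142 = 2.3 m.

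The positive sign of ρ is part of the assumption; a negative correlation would reverse the direction.

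**4. Between-group difference in the same setting.** Simulations with 150 per group, gains of 80 and 92 m, SD 40 and 15% loss in each group gave:
- Selective loss in one group and random loss in the other: retested-only bias of about 1.1 to 2.3 m, with a standard error of about 5 m.
- The same selection in both groups: bias between −0.1 and +0.2 m.
- Regression on baseline averaged over all categorized participants (the likelihood equivalent): bias within about ±0.2 m, standard error about 4.9 to 5.2 m, as for the unadjusted retested-only analysis.
- Baseline adjustment in retested participants only: between-group bias within ±0.15 m, standard error 4.5 to 4.9 m.

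Baseline adjustment alone therefore repairs the between-group contrast in this setting. Keeping the baseline-only participants is what repairs the within-group change.

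**5. Interaction with LOCF.** If baseline-only participants were admitted and LOCF still applied, each would be given zero change. With 15% of a group and a mean gain of 80 m, the mean change would be understated by 0.15 × 80 = 12 m, far more than the bias being corrected.

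**The case against.** The strongest reply has four parts.

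- **Expected loss is administrative.** Insurance cover may have little to do with walking gain, and then the bias is about 0. This stands: nothing in the article shows that loss is related to outcome or differs by group. The plan itself, however, allows for potentially non-ignorable dropout.
- **Most leavers may still be in mITT.** A reader might infer that everyone leaving before week 4 is lost unless the week-2 test was done. The article does not support that. The per-protocol rule accepts follow-up measurements from day 20, so someone leaving between day 20 and week 4 can have an end-of-stay test. The gap is mainly short stays without the optional test.
- **Sensitivity analyses are planned, and mITT with at least one follow-up is a common convention.** Their detailed method can properly be left to a fuller document. They do not change the fact that the two stated sets both leave these participants out.
- **The effect could be made to look much larger.** With p = 0.15 and D = 80 m, p × D is 12 m, which equals the planned difference if the 15% is read as a share of 80 m. A reader might infer that the whole target effect is at risk. That would need every lost participant to have no gain and no week-2 test or, for the between-group difference, a 15-point excess loss in one group. The article supports neither, and a likelihood fit assuming missing at random would not generally repair such loss.

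**Conclusion.** The point holds in a limited form. Participants with no repeat walk test are in neither stated prospective set, and they number at most roughly 15% of each group. The resulting bias is possible, not demonstrated. It is about 0 if loss is unrelated to gain. Under the assumed baseline-dependent loss, it is about 1.2 to 2.3 m in the within-group change, against an assumed gain of 80 m. It reaches a similar size between groups only if the selection acts in one group. That is small beside a between-group standard error of about 5 m. The reason to act is that the exclusion is unnecessary: an LMM with baseline as an outcome row can use these participants, and in the setting examined this removes the bias at no loss of precision compared with the unadjusted retested-only analysis.

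**What to change.** In Data analyses:

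1. Define the main set for the prospective LMM as all participants categorized to a study group who have a baseline value of the outcome, and delete the at-least-one-follow-up condition for that analysis.
2. Fit the LMM by (restricted) maximum likelihood with baseline as an outcome row, and state that LOCF is not applied in it.
3. Name this LMM as the primary analysis. Keep the retested-only set (with the t-tests, repeated-measures ANOVAs and LOCF) and the ≥20-day set as supportive.
4. Run the already planned non-ignorable-dropout sensitivity analysis on the full categorized set, because the likelihood fit corrects only loss explained by observed data.
5. Report the number without a retest in each group.

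The cost is a wording change and a small reanalysis of data already collected, with no new participants or visits. The downside is reliance on missing at random for the baseline-only participants, which is why item 4 is needed.
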